### Follow-up Assessment

At 1, 3, and 6 months, a blinded researcher will contact all study participants and help them complete a range of assessment tools relating to the primary and secondary outcome measures. They will be offered the opportunity to complete the assessments face-to-face or over the phone. Qualitative data collection will be in the form of a patient experience questionnaire and a focus group workshop, which will be conducted at 3 and 6 months. At 6 months, data related to each person’s clinic/program attendance rates and utilization of health services will be compiled from administrative records by the blinded researcher.

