## Methods

### Ethics and Dissemination

The study will be conducted per the Declaration of Helsinki (Hong Kong Amendment) and the Canadian guidelines for Good Clinical Practice. All participants will provide informed consent before study inclusion. The results will be disseminated at several levels, including participants, practitioners, academics/researchers, and health care organizations.

The study will be a prospective, parallel design, two-arm, rater-blinded randomized controlled pilot trial with a recruitment period of 12 months. It will involve active treatment for six weeks and an observation period of 6 months for each participant. An overview of the timeline for the project is in Table 1. The research will be carried out in an Addiction and Mental Health clinic in a large, sociodemographically diverse city in Western Canada (Edmonton, Alberta).

**Table 1 table1:** Gantt chart timeline.

Milestones		Year 1							Year 2			
		Q1	Q2		Q3		Q4		Q1		Q2	

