**Milestone 1: Recruiting and training of trainee in psychiatry, setting up of infrastructure for iCBT^a^**												
	1.1. Advertising and recruitment of a trainee in psychiatry who will support the research/evaluation of the project component, apply rTMS^b,^ and facilitate iCBT.	✓										

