### Outcomes

Outcome measures and time points are detailed in Table 2 and follow from the aim and objectives of the study. All measures (except patient experience questionnaire, interviews, and data extraction) are objective measures with published information regarding reliability and validity. The Hamilton Depression Rating Scale (HAM-D) [71,72] will be the primary outcome and all other measures will be secondary outcomes. These measures include the following: Columbia Suicide Severity Rating Scale (CSSRS) [73,74], Young Mania Rating Scale (YMRS) [75], Quick Inventory of Depressive Symptomatology Self Report-16 (QIDS SR-16) [76], Frequency, Intensity, and Burden of Side Effects Ratings (FIBSER; edited for rTMS) [77], Patient Rated Inventory of Side Effects (PRISE) [78], EuroQoL 5-Dimension 5-Level (EQ-5D-5L) [79,80], and World Health Organization Disability Assessment 2.0 (WHODAS 2.0) [81]. The primary outcome measure will be the mean change in the scores on the Hamilton Depression Rating Scale. Patient service utilization data and clinician-rated measures will also be used to gauge patient progress. Patient data will be analyzed with descriptive statistics, repeated measures, and correlational analyses. All quantitative data will be analyzed using SPSS (Version 26; IBM Corp) [82].

**Table 2 table2:** Client-oriented outcome measures.

Outcome measures				Time points assessed			
Variable type and construct		Tool	Rater	Baseline	1 month	3 months	6 months

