### Randomization and Blinding

A simple randomization technique will be used based on a single sequence of random assignments. A computer-generated Excel sheet (Microsoft Corp) will be used for simple randomization of subjects. Randomization will be stratified by using permuted blocks to ensure balance (1:1) between the two follow-up treatment groups. The randomization codes will be transmitted by an independent statistician via text message directly to a researcher’s password-protected phone line with a secure online backup. This will commence as soon as participants sign the consent forms.

As it will not be possible for participants to be blinded, treatment allocation will be made explicit to them as soon as randomization is concluded. Primary outcome assessors will be blinded to treatment group allocation by not involving them in discussions about study participants and not granting them access to the database that contains the randomization code. After data collection is complete, all data will undergo a blind review for the purposes of finalizing the planned analysis.

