### Patient and Public Involvement

This study was designed to address the clinical urgency to identify and respond to early evidence of treatment resistance using treatments that have proven efficacy in these more difficult-to-treat psychiatric patients. The study is designed as patient-oriented research with the active involvement of a patient representative who will be a coauthor of the study protocol. Our randomized trial offers participants the opportunity to provide feedback regarding the burden of the intervention through a focused group workshop involving a cross-section of participants from the two arms of the study.

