### Strengths of This Study

The strengths of this study include the following:

Randomization of participants will ensure that participants in the two treatment arms have somewhat similar psychiatric morbidity at baseline.Blinding of primary outcome assessors for the primary outcome measures will ensure the elimination of bias in outcome measures.

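### The blinded researcher also compiles 6-month attendance and service-use records that may show the arm, so blinding of the 6-month HAM-D is not secured by the tasks assigned

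*Protocol article*

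**What the plan says.** The first Ethics and Dissemination section under Methods describes a "two-arm, rater-blinded randomized controlled pilot trial". Randomization and Blinding gives two means of achieving this. The first is "Primary outcome assessors will be blinded to treatment group allocation by not involving them in discussions about study participants"; the second is to deny assessors the database that holds the randomization code. The same section says that participants are told their allocation.

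Follow-up Assessment has a blinded researcher contact every participant at 1, 3 and 6 months and help with the tools for the primary and secondary outcomes. It adds that at 6 months each person's "clinic/program attendance rates and utilization of health services will be compiled from administrative records by the blinded researcher".

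Three other places bear on the point:

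- Table 1, item 1.1, recruits a trainee "who will support the research/evaluation of the project component", who also applies rTMS and facilitates iCBT.
- Follow-up Assessment plans "a focus group workshop, which will be conducted at 3 and 6 months", and Patient and Public Involvement describes "a focused group workshop involving a cross-section of participants from the two arms of the study".
- Strengths of This Study states: "Blinding of primary outcome assessors for the primary outcome measures will ensure the elimination of bias in outcome measures". The Outcomes section says that the measures, a few apart, "are objective measures with published information regarding reliability and validity".

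**The concern.** Participants know their arm, and no attention control is described for the rTMS-alone arm. Blinding of the clinician rater is therefore the main protection of the primary outcome. Follow-up Assessment nevertheless hands the blinded person a data source that can carry the allocation. Keeping that person out of discussions and out of the randomization database does not help if the arm can be read from an attendance list.

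The article also wants this pilot to supply effect-size data for a full trial (Objectives; Discussion). A rating made with knowledge of the arm would pass its bias into that later sample size. The statement in Strengths of This Study would, in addition, lead readers to trust all the outcomes more than the design allows.

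**Working it through.** The article gives no figure to reproduce here. The check compares roles, tasks and timing, with simple counts.

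**1. Who does what.** Follow-up Assessment uses the label of blinded researcher for the person who helps with the primary and secondary tools and again for the person who compiles attendance. Table 2 lists the HAM-D as clinician-rated. The natural reading is that one person does both, though the article does not say so outright.

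**2. Do the safeguards reach this source?** There are two: no discussions about participants, and no access to the randomization database. Administrative attendance records are neither, so they are not covered.

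**3. Can attendance show the arm?** Inputs are from the Interventions section.

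- rTMS, both arms: 30 sessions over 6 weeks.
- iCBT in the clinic, combination arm only: 2 per week × 6 weeks = 12 sessions, which agrees with the 12 stated.
- Scheduled sessions: 30 with rTMS alone; 30 + 12 = 42 with the combination.
- Scheduled visit-days: 30 in each arm, because iCBT is given on rTMS days.

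A record of days attended would therefore not separate the arms. A record that itemises iCBT sessions would. An attendance rate that counts iCBT also needs a denominator of 42 in one arm and 30 in the other, so whoever computes it must know the arm.

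**4. Which ratings are exposed?** Post-baseline HAM-D ratings fall at 1, 3 and 6 months, which makes three. The compilation takes place at 6 months, so it can affect at most 1 of the 3, and only if it is done before that rating. The article gives no order.

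**5. Does assessor blinding eliminate bias in the outcome measures?** From the rater column of Table 2:

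| Rater | Tools | Count |
|---|---|---|
| Clinician | HAM-D, CSSRS, YMRS | 3 |
| Client | QIDS SR-16, FIBSER, PRISE, WHODAS 2.0, EQ-5D-5L | 5 |

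Thus 5 of 8 tools are completed by people who know their allocation. Blinding an assessor cannot remove bias from those five.

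**The case against.** The strongest reply is that the link from attendance to arm is an inference. In the Interventions section, similar wording about clinics and programs describes usual community care, which is open to both arms. Visit-days are equal, and nothing says that the administrative records itemise iCBT. This stands as a limit on certainty. It does not settle the matter, because the same article also uses the word program for the rTMS service and for MoodGYM, and it lists attendance separately from use of health services. The text allows the unblinding reading and does nothing to exclude it.

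Some stronger readings are tempting, and the documents do not support them.

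- *The trainee rates outcomes while delivering iCBT.* Table 1 says only that the trainee supports research and evaluation. Follow-up assessments go to a blinded researcher. The overlap is not excluded, but it is not stated either, and an article commonly leaves staffing detail to the full protocol.
- *The workshop unblinds the rater.* Nothing puts the rater in the workshop, and participants already know their arm. Exposure of rTMS-alone participants to MoodGYM through a workshop would be contamination, a separate question, and is speculative here.
- *The blinding has failed.* The documents show a risk that the assigned tasks leave open. They do not show a breach.
- *The bias can be sized against the 2.31-point rTMS-versus-sham difference in the Introduction.* The article does not name the scale of that difference, it concerns another comparison, and any rater shift would have to be assumed.

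On the self-rated scales, it is fair to reply that the article claims blinding only for raters and primary outcome assessors, labels the five tools as client-rated, and appears to use the word objective to mean validated. Those five scales therefore contradict no blinding claim. The sentence in Strengths of This Study is different: it claims that bias in outcome measures is eliminated, and that cannot be defended.

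**Conclusion.** The concern holds in a limited form. Blinding of the 6-month HAM-D is at risk and is not secured by the tasks assigned, because the blinded researcher is given a source that neither stated safeguard covers. The exposure is at most one of three post-baseline ratings. It rests on three assumptions: that the blinded researcher is the HAM-D rater or shares information with that rater, that the records itemise iCBT sessions, and that they are compiled before the 6-month rating. The article settles none of these. The size of any bias cannot be derived from the document.

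The claim that bias is eliminated is wrong without any such assumption, since 5 of the 8 listed tools are self-rated by unblinded participants.

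**What to change.** 1. In Follow-up Assessment, have existing staff who do not rate outcomes compile attendance and service use. Alternatively, let the blinded researcher do it only after that participant's 6-month HAM-D, CSSRS and YMRS are locked.
2. State that people who do not assess outcomes run the 3- and 6-month workshops.
3. State that the trainee who facilitates iCBT does not rate the HAM-D, CSSRS or YMRS.
4. In Strengths of This Study, replace the claim that bias is eliminated with a statement that assessor blinding is intended to reduce rater bias on the clinician-rated scales. Note there that the five client-rated measures are unblinded.

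The cost is one extraction task reassigned or slightly delayed, and a few sentences of text. No new staff are needed, and treatment does not change.

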### Patient and Public Involvement

This study was designed to address the clinical urgency to identify and respond to early evidence of treatment resistance using treatments that have proven efficacy in these more difficult-to-treat psychiatric patients. The study is designed as patient-oriented research with the active involvement of a patient representative who will be a coauthor of the study protocol. Our randomized trial offers participants the opportunity to provide feedback regarding the burden of the intervention through a focused group workshop involving a cross-section of participants from the two arms of the study.

### Ethics and Dissemination

The study will be conducted per the Declaration of Helsinki (Hong Kong Amendment) and Good Clinical Practice (Canadian Guidelines). Written informed consent will be obtained from each participant. The study has received ethical clearance from the Health Ethics Research Board of the University of Alberta (Pro00094208). The study is registered with ClinicalTrials.gov (registration number NCT04239651; preresult). The study results, expected 18 months after commencement of recruitment, will be disseminated at several levels, including participants, practitioners, academics/researchers, and health care organizations.

The investigator’s team will plan an organizational engagement strategy to advance discussions about practicability and effectiveness before the conclusion of the trial. This will help ensure the findings are a relevant part of decision-making processes in a way that is aligned with study findings as they emerge. This may facilitate the planning of a more extensive study that is endorsed at both leadership and operational levels so that the potential benefits of the interventions can reach participants in a timelier fashion.

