**Milestone 2: The recruitment of study participants**												
	2.1. Recruitment, baseline assessment, and randomization			✓		✓						
	2.2. Assignment into one of the two arms of the study			✓		✓						
	2.3. Delivery of iCBT and rTMS to participants			✓		✓		✓				

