**Milestone 3: Follow-up assessment of study participants**												
	3.1. Follow-up assessments of individual study participants							✓		✓		
	3.2. Follow-up satisfaction survey of participants, all groups							✓		✓		

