**Milestone 4: Data compilation, data analysis, and preparation of reports, publications, and presentations**												
	4.1. Data compilation			✓		✓		✓		✓		✓
	4.2. Data analysis			✓		✓		✓		✓		✓
	4.3. Preparation of reports, publications, and presentations											✓

^a^iCBT: internet-based cognitive-behavioral therapy.

^b^rTMS: repetitive transcranial magnetic stimulation.

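### Data analysis and discussion of effectiveness are scheduled while the trial is running, which conflicts with fixing the analysis by blind review after data collection

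*Protocol article*

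**What the plan says.** Three parts of the protocol article bear on when results are looked at.

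- **Table 1 (Gantt chart), Milestone 4.** The row "4.2. Data analysis" has five ticks, from Year 1 Q2 to Year 2 Q2. Data compilation has its own row (4.1) with the same five ticks. The row "4.3. Preparation of reports, publications, and presentations" is ticked only in Year 2 Q2.
- **Ethics and Dissemination (the later of the two sections with that heading).** The team will plan an "organizational engagement strategy to advance discussions about practicability and effectiveness before the conclusion of the trial". The stated purpose is for findings to enter decision-making "in a way that is aligned with study findings as they emerge".
- **Randomization and Blinding.** "After data collection is complete, all data will undergo a blind review for the purposes of finalizing the planned analysis".

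The same section says that participants know their allocation and that primary outcome assessors are blinded.

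**The concern.** A blind review is worth having because the people who settle the analysis do not yet know what it will show. That requires an order: collect, review blind, finalise, then compare the arms. Table 1 and the engagement plan allow a different order, with analysis under way from the first recruitment quarter and effectiveness under discussion before the end.

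Two things are at stake.

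- **The analysis.** If results by arm are known when the analysis is finalised, its choices can follow the results. Generating effect sizes for a full trial is a stated aim (Objectives; Discussion), so any such influence would carry into the design of that trial.
- **Trial conduct.** The trial runs in one clinic and participants know their arm. Those in the combined arm are helped through the iCBT sessions and encouraged to do more at home (Interventions). Table 1, item 1.1, gives one trainee research and evaluation support, rTMS delivery and iCBT facilitation. Emerging results could therefore reach someone who delivers the treatment and affect recruitment or encouragement.

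**Working it through.** There is no planned figure to reproduce: the article states no alpha, power or interim test, and the sample of 100 is set by resources. The check compares the timing statements.

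**Step 1. Read Table 1 by column position.** In the extracted text, each quarter after Year 1 Q1 spans two columns. The order of the rows relative to one another does not depend on that reading.

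| Row | Ticks |
|---|---|
| "2.1. Recruitment, baseline assessment, and randomization" | Year 1 Q2, Q3 |
| "3.1. Follow-up assessments of individual study participants" | Year 1 Q4, Year 2 Q1 |
| "4.2. Data analysis" | Year 1 Q2, Q3, Q4, Year 2 Q1, Q2 |
| "4.3. Preparation of reports, publications, and presentations" | Year 2 Q2 |

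**Step 2. Compare with the end of data collection.** The last follow-up tick is Year 2 Q1. Of the five analysis ticks, four (Year 1 Q2, Q3, Q4 and Year 2 Q1) fall in or before that quarter. Only Year 2 Q2 clearly follows it. The count uses Table 1 as drawn. The Methods section gives a 12-month recruitment period; if that ran from Year 1 Q2 to Year 2 Q1, six further months of follow-up would end in Year 2 Q3, and all five ticks would precede completion.

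**Step 3. Ask whether row 4.2 could mean only data handling.** Compilation is listed separately as 4.1, so 4.2 is meant as something more. It could still be descriptive, pooled or qualitative; the table does not say.

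**Step 4. Ask whether the engagement plan supplies the limit.** It does not. It names effectiveness alongside practicability and ties the process to study findings. In a two-arm trial whose goal is comparative effectiveness, that wording permits a by-arm reading without stating one.

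**Step 5. Set this against the blind review.** If early work is pooled or about feasibility, all three statements can be followed. If it includes outcomes by arm, the review after data collection is not blind. The text allows both readings, so the passages need reconciling.

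**Step 6. Illustration of size, under assumptions the article does not make.** Suppose the arms were tested at each of K equally spaced looks at an unadjusted two-sided 5%, and a rejection at any look counted as positive. With independent standard normal increments X, the statistic at look k is Z_k = (X_1 + … + X_k)/√k, and the error rate is P(|Z_k| > 1.96 for some k ≤ K) under no effect. Simulation with 2,000,000 runs gives:

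| Looks K | Overall false-positive rate |
|---|---|
| 1 | 5.0% |
| 2 | 8.3% |
| 3 | 10.7% |
| 4 | 12.6% |
| 5 | 14.2% |

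Table 1 first schedules follow-up in Year 1 Q4, so the quarters with both an analysis tick and scheduled follow-up outcomes are Year 1 Q4, Year 2 Q1 and Year 2 Q2. That makes K = 3, or about 11%.

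**The case against.** The strongest reply is that nothing in the article says outcomes by arm will be tested or circulated during the trial. Early ticks on a coarse quarterly chart may stand for descriptive statistics, or for the patient experience questionnaire and focus group work that begins at 3 months. The stated release times are late: reporting is ticked only in Year 2 Q2, and results are expected 18 months after recruitment starts. This stands, and it is why the point is a conflict in wording rather than a demonstrated breach.

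A reader might infer more: five unadjusted looks and a 14% false-positive rate. The documents do not support that. Table 1 has no follow-up scheduled in the first two analysis quarters, no interim test or decision rule is stated, and a look without a decision rule does not change the error rate of the final test. A reader might also infer that leadership will receive interim results. Leadership is named only as a level that may endorse a larger study. Nor is the absence of interim error control a fault in itself, since an analysis plan that is not shown may deal with it.

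Ratings of the primary outcome also have some protection. Assessors are kept out of discussions about participants and away from the randomization code, and a blinded researcher does the follow-up. These safeguards do not cover those who deliver treatment or those who finalise the analysis.

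What the reply does not remove is that effectiveness is named, before the end of the trial, with no limit to pooled data. Access rules in another document would still leave these statements to be reconciled.

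**Conclusion.** The concern holds as a conflict between stated plans. Analysis is scheduled from the first recruitment quarter and effectiveness is to be discussed before the trial ends, while the analysis is to be finalised blind after data collection. The harm is conditional: it arises if outcomes by arm are analysed or discussed early, which the text permits but does not state. In that case the blind review loses its purpose and trial conduct may be influenced.

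No false-positive rate should be attributed to the plan. The figure of about 11% illustrates three looks, and rests on an assumed unadjusted two-sided 5% test at each one and on any rejection counting as positive. For a pilot of this kind the wording should be changed, and the change is cheap.

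**What to change.** 1. **Table 1, row 4.2.** Place comparative (by-arm) outcome analysis after the last 6-month visit, the blind review and database lock. On the chart as drawn, that leaves Year 2 Q2.
2. **Before that point.** Keep row 4.1 (data compilation) running. Allow only pooled, arm-blind checks of recruitment, retention and data quality, plus the qualitative feasibility work, and say so in the text beside the blind-review sentence.
3. **Ethics and Dissemination.** Reword the engagement plan so that discussion before completion covers practicability and feasibility, and comparative effectiveness is shared only after lock.

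The cost is an edit to one table row and about two sentences. The downside is that the organisation sees effectiveness results only at the end; early engagement on feasibility is kept.
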